# Feasibility of diabetes self-management coaching program for individuals with type 2 diabetes in the Ethiopian primary care setting: a protocol for a feasibility mixed-methods parallel-group randomized controlled trial

**DOI:** 10.1186/s40814-024-01487-3

**Published:** 2024-04-08

**Keywords:** Feasibility, Diabetes, Self-management, Coaching, RCT, Primary care, Ethiopia

## Abstract

**Background:**

Diabetes mellitus is the third most prevalent chronic metabolic disorder and a significant contributor to disability and impaired quality of life globally. Diabetes self-management coaching is an emerging empowerment strategy for individuals with type 2 diabetes, enabling them to achieve their health and wellness goals. The current study aims to determine the feasibility of a diabetes self-management coaching program and its preliminary effectiveness on the clinical and psychosocial outcomes in the Ethiopian primary healthcare context.

**Methods:**

The study will employ a mixed-method feasibility randomized controlled trial design. Forty individuals with type 2 diabetes will be randomly allocated to treatment and control groups using block randomization. The primary feasibility outcomes include acceptability, eligibility, recruitment, and participant retention rates, which will be computed using descriptive analysis. The secondary outcomes are self-efficacy, self-care activity, quality of life, and glycated hemoglobin A1c. For normally distributed continuous variables, the mean difference within and between the groups will be determined by paired sample Student *t*-test and independent sample Student *t*-test, respectively. Non-parametric tests such as the Mann-Whitney *U* test, the Wilcoxon signed rank test, and the Friedman analysis of variance test will determine the median difference for variables that violated the normality assumption. A repeated measure analysis of variance will be considered to estimate the variance between the baseline, post-intervention, and post-follow-up measurements. A sample of 10 volunteers in the treatment group will participate in the qualitative interview to explore their experience with the diabetes self-management coaching program and overall feasibility. The study will follow a qualitative content analysis approach to analyze the qualitative data. Qualitative and quantitative findings will be integrated using a joint display technique.

**Discussion:**

Evidence reveals diabetes self-management coaching programs effectively improve HbA1c, self-efficacy, self-care activity, and quality of life. This study will determine the feasibility of a future large-scale randomized controlled trial on diabetes self-management coaching. The study will also provide evidence on the preliminary outcomes and contribute to improving the diabetes self-management experience and quality of life of individuals with type 2 diabetes.

**Trial registration:**

The trial was registered online at ClinicalTrials.gov on 12/04/2022 and received a unique registration number, NCT05336019, and the URL of the registry is https://beta.clinicaltrials.gov/study/NCT05336019.

**Supplementary Information:**

The online version contains supplementary material available at 10.1186/s40814-024-01487-3.

## Introduction

Diabetes is one of the leading global causes of morbidity and mortality [1]. The prevalence of diabetes is increasing at alarming rates,according to the [2] International Diabetes Federation (IDF) report, more than half a billion people live with diabetes globally, and this number will increase to 783.2 million by 2045 [3]. Approximately 80% of individuals with diabetes live in low- and middle-income countries (LMIC) [4, 5] and Ethiopia is one of the four African countries with the highest population of adults with diabetes [6]. According to IDF IDF [2], the IDF reported the prevalence of diabetes in Ethiopia is 3.3%. A systematic review and meta-analysis study in 2021 found a 6.5% pooled prevalence of diabetes in Ethiopia, ranging between 2% in the Tigray region and 14% in Dire Dawa [7]. Ethiopia does not have evidence-based national diabetes guidelines or standard referral criteria for diabetes management [8]. As a result, individuals with diabetes may receive substandard care. Notably, a systematic review and meta-analysis study revealed more than half of individuals with type 2 diabetes have poor self-care practices [9]. Furthermore, many people with type 2 diabetes in Ethiopia visit traditional healers and religious therapies like holy water to get a cure for diabetes mellitus [10] which makes self-management challenging.

An earlier cross-sectional study conducted in Addis Ababa, the capital of Ethiopia, showed that 87% of diabetic patients had regular clinical follow-up; however, 75% of participants required hospital admissions and did not receive diabetic education, and 95% of patients failed to monitor their blood glucose regularly [11]. A recent population-based cross-sectional study from Addis Ababa found that three-fourths of individuals with type 2 diabetes have glycated hemoglobin A1c (HbA1c) > 7.0% [12], indicating ongoing poor diabetes self-management. Furthermore, another hospital-based cross-sectional study in Southern Ethiopia revealed that 50% of individuals with diabetes suffered from one or more chronic complications: of these, 35%, 25%, and 15% acquire neuropathy, retinopathy, and nephropathy, respectively [13].

Although self-management is often used interchangeably with self-regulation, self-care, patient education, and patient counseling, it is beyond merely providing information and increasing awareness [14]. Self-management is recognized as tertiary prevention aiming to prevent the deterioration of health among individuals with chronic illness [14]. Self-management programs enable individuals to be active, responsible, informed, and autonomous in managing chronic illness’s physical, social, and emotional impact through collaboration with family, friends, and the healthcare provider(s) [15].

In recent years, Diabetes Self-Management (DSM) coaching, also called diabetes health coaching, has demonstrated a substantial effect on improving health [16]. The DSM coaching is a client-centered empowerment approach that enables individuals to self-manage diabetes (Radwan, [17]. It focuses on individual preferences, experiences, and values and engages participants in decision-making [18]. Studies in Taiwan, Indonesia, and Canada found that diabetes health coaching interventions can significantly improve HbA1c [19–21]. Systematic review and meta-analysis studies also demonstrate diabetes health coaching is an effective strategy to improve HbA1c [16, 17, 22, 23]. In addition, evidence suggests diabetes health coaching can lead to improvements in self-efficacy [24], self-care practice [19, 20], and quality of life [22, 25]. Despite the above evidence, culturally appropriate and effective DSM programs are lacking in most LMICs (Iregbu & Iregbu, [26], including Ethiopia.

In Ethiopia, an effective, patient-centered empowerment strategy to enhance diabetes self-management, build self-efficacy, improve quality of life, and control blood glucose is lacking, notably in the primary care setting. The DSM coaching program, which shows promising health outcomes in different settings, could be a practical approach in the primary care context of Ethiopia. Hence, the study will adapt a DSM coaching program from an evidence-based health coaching intervention [20] informed by an I-change model [27]. The study’s overarching goal is to determine the feasibility of implementing the DSM coaching program among individuals with type 2 diabetes in the primary care setting of Ethiopia and assess the program’s preliminary effectiveness in improving behavioral and clinical outcomes.

## Methods and materials of the study

### Primary objective

To determine the feasibility and acceptability of implementing an adapted DSM coaching program for individuals with type 2 diabetes in Ethiopia’s primary care settings.

### Secondary objective

To evaluate the potential effectiveness of the DSM coaching program on self-care activity, self-efficacy, quality of life, and HbA1c among individuals with type 2 diabetes.

### Phases of study

The study will have three phases: adaptation, implementation, and evaluation of the DSM coaching program.

#### Phase I: Adaptation of the DSM coaching intervention

This study will adapt an evidence-based intervention informed by the I-change model [20]. A purposively selected panel of experts will be invited to participate in adapting the DSM coaching program through the recommendation of selected departments. The Principal Investigator (PI) will ask the selected professionals to participate in the intervention adaptation process through a formal letter. A panel of multidisciplinary teams consisting of ten professionals and a patient representative will sit together to discuss and adapt the DSM coaching program and fidelity assessment tool at three-panel discussions.

The adaptation team will include one nurse, one internist (senior specialist doctor), two nurse researchers, two occupational therapists, two public health nutritionists, one physiotherapist, one epidemiologist (chronic disease researcher), and a patient representative.

The adaptation process will be iterative and will take 4 months. Panel members will review the candidate intervention manual before the panel discussion. The first panel discussion will focus on collecting feedback on the intervention component, reviewing each intervention component, and selecting potential intervention components for the DSM coaching program. A nominal group technique will be used to reach a consensus among panelists [28]. Accordingly, panelists will discuss thoroughly each intervention component based on the merits and demerits of incorporating it into the manual. Panel members will vote on the inclusion or exclusion of the intervention component and justify their decision. A consensus will be reached by a majority vote and supported by justification. The second panel discussion will emphasize revising selected intervention components and delivery methods. Two individuals with type 2 diabetes will participate in the adaptation process. During the third panel discussion, the panel members will review the draft DSM coaching intervention manual and approve the document. Furthermore, the adaptation process will use expert opinion and rating feedback to identify potential intervention components and delivery methods. The research team will prepare the content of the DSM coaching intervention manual by reviewing the literature and feedback from experts and the target population.

#### Phase II: Feasibility RCT

##### Study design

A convergent mixed-methods, single-blind feasibility randomized controlled trial (RCT) will be employed to assess the feasibility of the DSM coaching program. The study will adhere to the SPIRIT guideline for pilot and feasibility randomized trials [29]. The trial was registered online at ClinicalTrials.gov on 12/04/2022, and registration number NCT05336019 was received.

##### Study setting

The study will be conducted in the primary care settings of Gondar City, Amhara region, Ethiopia. Gondar City is about 740 km away from Addis Ababa, the capital of Ethiopia [30]. Christianity is the dominant religion, followed by Islam. The most common staple diet in Ethiopia is Injera, made up of teff flour after a consecutive date of fermentation. Almost all Ethiopians eat Injera with a stew of lentils or meat at least once daily [31]. People consume organic food items due to limited access to processed food items. Fasting is a common practice during Lent and Ramadan,hence, the study period will exclude these seasons. Gondar City has one referral hospital, nine primary care centers, and additional private health facilities.

According to unpublished Gondar City Health District reports, more than 10,000 individuals attend regular diabetes clinics in Gondar City health facilities. Individuals with diabetes received diabetes care at the referral hospital, private clinics, and primary care health centers. The hospital serves more than 2600 diabetes patients in the chronic disease clinic, and around 1312 patients have type 2 diabetes [32]. The hospital is a point of referral for newly diagnosed individuals with diabetes from health centers, individuals with complicated diabetes, and individuals with uncontrolled diabetes. Because of the absence of a district or a zonal hospital in the city, the city’s health system is inconsistent with the national referral system. As a result, the hospital provides primary, secondary, and tertiary care for individuals with diabetes. Most individuals with uncontrolled diabetes bypass the health centers and get care at the hospital. In addition, health centers also refer uncontrolled diabetes cases to the hospital. As a result, the study subjects will be recruited from the hospital. The research assistant will take informed consent from volunteers with type 2 diabetes who fulfill the screening criteria. Once the recruitment and baseline assessment are completed, the intervention will be administered in the selected health centers.

### Participant eligibility

#### Inclusion criteria

The study includes individuals who have been attending the diabetes clinic for at least 6 months, are living in Gondar City, are taking anti-diabetic medications, have a recent HbA1c ≥ 7% (within 3 months), and are between 18 and 65 years old.

#### Exclusion criteria

The study will exclude individuals with clinically confirmed mental illness, pregnancy [33], and cardio-vascular diabetes complications (neuropathy, nephropathy, retinopathy, stroke, gangrene, cancer, and cardiovascular disease). Individuals who are seriously ill and hospitalized during screening will also be excluded. Furthermore, as the DSM coaching program demands participants be physically active, individuals with physical impairment (visual deficit, hearing deficit) and lower extremity amputation or palsy will be excluded.

#### Sample size determination

A formal sample size calculation will not be applied for a feasibility RCT study [34]. Hertzog [35] suggests that a sample size of 10–40 participants per group is enough for feasibility studies (Hertzog, [35]. Hence, considering the study’s pilot nature, the intervention’s high intensity, and the limited research fund, we will recruit 40 participants. Twenty participants will be allocated to each arm of the study with a 1:1 ratio.

### Participant recruitment procedure

A 3-min audio record that briefly explains the purpose of the study and the recruitment process will be prepared in Amharic and played in the waiting area of the chronic disease clinic during working hours. In addition, a 1.5 m × 2 m poster describing the study objectives and the recruitment process will be prepared in Amharic and displayed in the waiting area. Nurses in the chronic disease clinic will receive a half-day training about the study, the screening material, and how to connect eligible individuals with the research assistant. Nurses working in the clinic will screen all individuals with type 2 diabetes and connect them with the research assistant. The research assistant will meet eligible individuals in a separate office in the clinic to discuss the study participation, information sheet, and informed consent.

### Randomization, allocation, and blinding

Participants will be assigned to the treatment and control groups using a block randomization technique with a block size of four [36]. An external researcher with no other role in the study will manually generate the random allocation sequence [37]. From a block of four, six possible combinations using treatment “T” and control “C” will be generated (TTCC, TCTC, TCCT, CCTT, CTTC, and CTCT). A nurse working outside the chronic disease clinic will draw the lottery 10 times from these six potential combinations to allocate 40 participants. The external researcher will document the sequence drawn by the nurse and prepare 40 opaque sealed envelopes to conceal the group allocation [37, 38]. The research assistant will receive the prepared envelopes, randomly allocate participants by opening the envelope in front of the participant, and inform participants of their allocation. All participants will be registered in the master linkage log sheet and informed of the next meeting date.

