#### Blinding

Because of the nature of the intervention, it is impossible to mask study participants and the interventionist. However, the study assessors will be masked to the group allocation. To prevent accidental disclosure by study participants, the research assistant will provide a 5-min orientation for each participant just before each data collection period. To ensure the blinding of the assessors, three data collectors who are academic staff at the University of Gondar will be recruited for each assessment time (T1, T2, and T3). One data collector will be assigned for each phase and will not have contact with the study data and participants.

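### The unblinded research assistant who takes consent also opens fixed blocks of four one participant at a time, so allocation is open to prediction, and the order of allocation and the T1 interview is not stated

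*Protocol article*

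**What the plan says.** **Sequence.** Under Randomization, allocation, and blinding, "Participants will be assigned to the treatment and control groups using a block randomization technique with a block size of four". The six possible blocks are listed ("TTCC, TCTC, TCCT, CCTT, CTTC, and CTCT"). An external researcher is responsible for the sequence, and a nurse from outside the clinic is to "draw the lottery 10 times from these six potential combinations to allocate 40 participants". The allocations go into opaque sealed envelopes. Sample size determination adds: "Twenty participants will be allocated to each arm of the study with a 1:1 ratio".

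**Who enrols and who allocates.** Clinic nurses screen. Under Participant recruitment procedure, "The research assistant will meet eligible individuals in a separate office in the clinic to discuss the study participation" and consent, and Study setting confirms that this assistant takes consent. The same assistant is then to "randomly allocate participants by opening the envelope in front of the participant, and inform participants of their allocation". Strengths and limitations of the study lists the research assistant among those who are not blinded.

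**Timing.** Study setting says: "Once the recruitment and baseline assessment are completed, the intervention will be administered in the selected health centers". No sentence places allocation before or after the T1 interview. Under Blinding, to guard against disclosure, "the research assistant will provide a 5-min orientation for each participant just before each data collection period", and a separate masked assessor is assigned to each of T1, T2 and T3.

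**The concern.** Opaque envelopes hide the next assignment, but they do not stop it being deduced from the ones already opened. In a fixed block of four, the last place is always determined, and the last two are determined when the block opens with two of the same arm. The person holding the consent conversation has seen all earlier results and could, even without intending to, let the expected arm influence who is enrolled and when. That bears on the comparability of the arms. It also bears on the recruitment rate, which is a primary feasibility outcome with a progression criterion in Table 1.

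The second issue is baseline measurement. Self-care activity, self-efficacy and quality of life are self-reports given to an interviewer. If participants already know their arm at T1, disappointment or expectation can shift the answers. Those values then feed the within-group comparisons, the baseline comparison and, if it is used, the adjustment for pretest score in Data analysis and management.

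**Working it through.** **Reproducing the plan's figure.** 10 blocks × 4 = 40 participants; 10 × 2 = 20 per arm. Both agree with the article.

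**Predictability.** Inputs: block size 4, the six listed blocks taken as equally likely, ten blocks. A place is certain when one arm's two places in the block are already used. The best guess is the arm with more places left, or a coin toss when they are equal.

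| Block | Certain places | Expected correct guesses |
|---|---|---|
| TTCC, CCTT | 2 each | 0.5 + 0 + 1 + 1 = 2.5 each |
| TCTC, TCCT, CTTC, CTCT | 1 each | 0.5 + 1 + 0.5 + 1 = 3 each |

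- Certain per block: (2×2 + 4×1)/6 = 8/6 = 1.33 of 4, or 33.3%.
- Over ten blocks: 13.3 of 40 expected. The possible range is 10 (one per block) to 20 (two per block).
- Correct guesses per block: (2×2.5 + 4×3)/6 = 17/6 = 2.83 of 4, or 70.8%. Over ten blocks this is 28.3 of 40, against 20 by chance.

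**Would mixed block sizes be enough?** Simulation (3,000 runs) of an observer who knows the set of sizes but not the size of each block:

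| Sizes | Certain, of 40 | Best guess correct |
|---|---|---|
| 4 and 6 | 2.3 (6%) | 69% |
| 2, 4 and 6 | 1.5 (4%) | 70% |

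Mixing sizes removes most of the certainty but almost none of the guessability.

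**Would a single list of 20 T and 20 C be better?** If recruitment stopped at the 32 named in Table 1, the arms would differ by 4 or more when the 8 unused places hold at most 2, or at least 6, of one arm. The probability is 2 × [C(20,0)C(20,8) + C(20,1)C(20,7) + C(20,2)C(20,6)] / C(40,8) = 2 × 9,040,770 / 76,904,685 = 0.235, about 24%. Eight complete blocks of four give exactly 16:16.

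**Is the arm known at T1?** The text has to be read together.

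- Pointing to allocation first: the non-disclosure orientation precedes every data collection, and Data collection gives its purpose as keeping the group from the interviewer; the T1 assessor is to be masked; Table 1 and Recruitment rate count a person as recruited once randomized, and Study setting names recruitment before baseline assessment; after allocation, participants are given their next meeting date.
- Leaving it open: no sentence gives the order; Table 2 puts recruitment and the T1 measures together at week 0; Fig. 1, the participant flow diagram, is not available in the text reviewed.

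**The case against.** **The predictability is conditional.** The assistant must know or infer the block size, take the envelopes in sequence, and allocate each person before consenting the next. The article does not say that the assistant is told the block size, and the sequence is prepared by someone outside the study. Numbering the envelopes and withholding the block size are details that a condensed article may leave to the full protocol. This stands, so 13.3 of 40 is a ceiling. It does not dissolve the point: someone who sees every allocation can infer a fixed block of four, and a free choice among unnumbered envelopes would be a different weakness, not a safeguard.

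**The scope for selection is limited.** Nurses do the screening, several criteria are recorded facts such as age, residence and HbA1c, and the coach is the principal investigator, not the assistant. This also stands. What remains exposed is mainly the consent conversation.

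**The baseline point is an inference.** The orientation and the separate assessors may be one uniform procedure described once for all three time points. That is possible, though allocation first is the more natural reading. A reader might infer that all 40 baselines are definitely post-randomization. The documents do not establish that, and HbA1c comes from chart review, so only the three interview scales could be affected. Adjustment for the pretest score is itself only to be considered, if a group difference is detected.

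**This is a small feasibility trial.** Effect estimates are secondary and preliminary. True, but recruitment is a primary outcome, and the Discussion says the evidence will be used to design the definitive trial, so the procedure may be carried forward.

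**Conclusion.** The point holds in conditional form. It is stated that one unblinded person takes consent and opens envelopes from fixed blocks of four, one participant at a time. For a recruiter meeting the three conditions above, the expected number of allocations known in advance is 13.3 of 40 (33%; range 10 to 20), and the best-guess rate is 70.8%. A reader might conclude that a third of allocations will in fact be foreseen, or that selective enrolment will follow. The documents support neither; they show only that the procedure as written does not prevent it.

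That participants know their arm at T1 is likely on the text but not stated. If they do, the self-care, self-efficacy and quality-of-life baselines are post-allocation values. If T1 comes first, that part falls away and the predictability remains. Neither the direction nor the size of any resulting bias can be derived from the documents. The change is worth making because it is nearly free and removes both problems.

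**What to change.** 1. State the order explicitly: consent, T1 interview, then allocation.
2. Keep the ten drawn blocks of four and place them in sequentially numbered envelopes.
3. Open the envelopes in enrolment order only after the last participant has consented and completed T1, and tell participants their arm then. The article already holds back coaching until recruitment and baseline are complete, so this does not delay the intervention.
4. Report the numbers eligible, consented, and randomized separately, and say how the two-month window in Table 1 applies to each.

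Once everyone has consented and completed T1 and the envelope order is fixed, predicting the next arm no longer helps anyone influence enrolment. There is then no need for mixed block sizes or a single 20/20 list, and keeping fours holds the arms within 2 of each other if fewer than 40 enrol.

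**Cost.** No additional staff or materials beyond numbering the envelopes. Participants learn their arm later. Anyone lost between consent and allocation lowers NR in the recruitment rate NR/NE, which is why step 4 is needed to keep that primary outcome interpretable.
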